### Economic analysis

The economic analysis within this trial will consist of an extensive cost analysis of both the control and intervention groups from the NHS perspective, and will identify the key items (if any) that underpin any significant cost differences between the two trial groups. A societal perspective on costs will also be taken to include costs that fall on the patients, their carers/families and/or non-NHS cost centres that result from the different treatment regimes. Data will be gathered through the administration of the Participant Costs Questionnaire (see online supplementary appendix S2), which was designed specifically for this study, and may be the first of its type to be published. This latter work will complement the main NHS perspective of the cost analysis. In terms of effectiveness, health-related QoL data based on the SF-36 collected at three time points in the trial's follow-up will be analysed using the SF-6D algorithm^17^ to produce utility scores. Utility scores based on SF-36 will also be compared against absolute utility scores derived from the EQ-5D^23^ collected at the 6-month follow-up. Depending on what the data show, and what realistic assumptions we can make, we may proceed to a cost-utility analysis and undertake extensive probabilistic sensitivity analysis.^24^

### Trial management

Day-to-day running of the trial will be overseen by a TMG, comprising, as a minimum, the Chief Investigator, Senior Trial Manager, Trial Manager, Trial Statistician and Data Manager. TMG meetings will take place on a regular basis throughout the duration of the study. The TMG will have responsibility for ensuring the compliance and progress of the study in relation to all regulatory, administrative academic and any clinical or safety issues.

### Trial monitoring and oversight

Monitoring of study conduct and data collected will be performed by a combination of central review and site monitoring visits to ensure the study is conducted in accordance with the International Conference on Harmonisation Good Clinical Practice Guidelines. Study site monitoring will be undertaken by the Newcastle Clinical Trials Unit.

As agreed by the sponsor, a TOC will adopt the joint roles of Trial Steering Committee (TSC) and Data Monitoring and Ethics Committee (DMEC), with independent members meeting in a closed session to fulfil the DMEC role. The TOC will consist of the Chief Investigator, an independent Chair/clinician, the Trial Statistician, independent lay representative and the TMG; a representative of the funder will be invited to attend. The purpose of this committee will be to monitor efficacy and safety end points, although only independent members will have access to un-blinded study data. A written charter will be agreed and used by the TOC.

After 6 months of recruitment, initial rates of recruitment will be used to project total recruitment, to ensure sufficient participants to power the trial. The TOC will advise on whether to continue or discontinue the study and make a recommendation to the sponsor. The trial may be prematurely discontinued on the basis of new safety information, or for other reasons given by the TOC, sponsor, regulatory authority or research ethics committee. If the study is discontinued prematurely, active participants will be informed, and no further participant data will be collected.

### Adverse event reporting

The participants recruited into this study are critically ill with a high likelihood of significant morbidity and mortality. Many will have life-threatening conditions, and we expect that a large proportion of the participants will experience Adverse Events (AE) and Significant Adverse Events (SAE) during the time between randomisation and discharge from Critical Care. For this reason, the time period for AE and SAE reporting will begin with each sedation hold (if performed), continue through each physiotherapy session, and end 30 min after the end of each physiotherapy session. All adverse events occurring during the reporting period will be recorded on an AE/SAE Report Form, and categorised as to the degree of expectedness, relatedness and severity. All SAEs that occur during the reporting period must be reported to the Chief Investigator within 24 h of learning of the event, and a completed report form sent to the Trial Manager. An SAE occurring to a research participant should be reported to the main research ethics committee where, in the opinion of the Principal Investigator, the event was related to administration of any of the research procedures and unexpected (ie, not listed in the protocol as an expected occurrence). A confirmed, related SAE will be reported to the research ethics committee within 15 days of the Chief Investigator becoming aware of the event. In addition, the trial sponsor will be notified of the SAE.

There are a number of AEs that may be expected to occur in patients undergoing physiotherapy in Critical Care and do not need to be reported, these are: MAP <65 mm Hg; HR<40 or >130 bpm; respiratory rate <5 or >40 breaths/min; marked ventilator asynchrony; oxygen saturation <88% or, if known respiratory disease, a 10% decrease from normal oxygen saturation; marked ventilator asynchrony; patient distress; new cardiac arrhythmia; myocardial ischaemia; insecure airway; fall to knees.

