### Study design

We will conduct a multicentre patient randomised, parallel group, controlled trial comparing two intensities of physiotherapy on physical QoL. Adult, critically ill patients, ventilated for more than 48 h, will be randomised to the control or intervention group (figure 1). The control group will receive usual physiotherapy, including a once-daily functional retraining session (Monday to Friday). The intervention group will receive a more intensive physiotherapy programme, including at least one functional retraining session per day (Monday to Friday) and an individualised structured exercise programme.

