**Figure 4 BMJOPEN2015008035F4:**
[figure not shown]
Strengthening programme algorithm.

The control group will receive the standard intensity of physiotherapy which is normally given on participating units. This will consist of no more than 30 min of active exercise comprising: functional retraining (figure 3) and, if time permits, an individually tailored exercise programme, based on a muscle-strengthening algorithm (figure 4). Physiotherapy will occur from Monday to Friday as there is no physiotherapy service available routinely at weekends.

The intervention group will receive an augmented programme with a target delivery of 90 min of active exercise per day, again from Monday to Friday. The physiotherapy sessions will consist of functional retraining (figure 3) and an individually tailored exercise programme, based on a muscle-strengthening algorithm (figure 4). The delivery of this treatment will be divided into one or more sessions depending on: the individual participant's tolerance of the programme; the need for other medical and nursing interventions; and the progression of the participant's recovery.

During the physiotherapy sessions, participants will be monitored closely, and if any of the following occur, the session will be stopped: MAP <60 mm Hg; heart rate <40 or >130 bpm; oxygen saturation <88% (or, if known respiratory disease, a 10% decrease from normal oxygen saturation); marked ventilator asynchrony; participant distress; new arrhythmias; myocardial ischaemia; concern for airway integrity; endotracheal tube removal; fall to knees; or any other significant event where the participant is unable to continue rehabilitation.

Apart from the difference in the intensity of physiotherapy, both groups will have the usual rehabilitation pathway in participating units.

Following discharge from Critical Care, both groups will receive the same, standard intensity of ward-based physiotherapy, and continue with their rehabilitation pathway. In line with NICE guidance, participants will receive an exercise diary to continue independently on discharge from hospital. Any patient readmitted to Critical Care will receive standard physiotherapy care during the second and any subsequent readmissions. All readmissions will be recorded.

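### Adverse events are collected only around physiotherapy sessions, so observation time is longer by design in the intervention arm, and the reporting rule for listed events contradicts itself

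*Protocol article*

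**What the plan says.** Under Adverse event reporting, the protocol explains that these patients will have many events before they leave Critical Care, and for that reason restricts collection: "the time period for AE and SAE reporting will begin with each sedation hold (if performed), continue through each physiotherapy session". Collection stops half an hour after each session is over.

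The amount of physiotherapy differs by arm. Under Study intervention, control has a ceiling ("This will consist of no more than 30 min of active exercise") and intervention has a target ("an augmented programme with a target delivery of 90 min of active exercise per day"), given in one or more sessions. Study design describes control as "usual physiotherapy, including a once-daily functional retraining session (Monday to Friday". Sedation is managed alike in both arms.

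On what is collected inside the window, the section says "All adverse events occurring during the reporting period will be recorded on an AE/SAE Report Form" and requires every SAE in the window to go to the Chief Investigator within 24 h. It then lists events that may be expected in patients "undergoing physiotherapy in Critical Care and do not need to be reported". The list includes new arrhythmia, myocardial ischaemia, insecure airway and fall to knees.

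**The concern.** There are two separate problems.

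First, the length of the observation window depends on the treatment being tested. More minutes lengthen it, and each extra session adds its own 30-min tail. The protocol expects frequent events from the underlying illness, so a longer window picks up more coincidental events even if physiotherapy does no harm. A higher raw count in the intervention arm could not be read as harm. Events outside the windows are not collected as AEs, so later analysis cannot recover them.

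Second, the rules inside the window conflict. A site could record a listed event because all AEs are recorded, or omit it because it is on the list. Nothing says what happens when a listed event is serious. If sites omit listed events, the safety data would lack most of the events that the protocol itself treats as reasons to stop a session.

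The two problems can push in opposite directions, so neither an excess nor equality in raw counts would be interpretable by the oversight committee or in the final report.

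**Working it through.** **Window length.** The protocol states no window length or ratio, so there is no figure of its own to reproduce.

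Inputs from the protocol:
- Tail after each session: 30 min (Adverse event reporting).
- Control active exercise: at most 30 min a day (Study intervention); one daily functional retraining session (Study design).
- Intervention active exercise: 90 min target, one or more sessions, no maximum number (Study intervention).

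Assumptions, because the protocol gives no figure:
- P, the minutes from the start of the sedation hold to the session: 0 to 180, the same in both arms.
- k, the number of intervention sessions: 1 to 3.
- Session length equals active minutes.

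For a full active-therapy weekday with one control session:

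ratio = (P + 90 + 30k) / (P + 30 + 30)

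| P (min) | Control window | k = 1 | k = 2 | k = 3 |
|---|---|---|---|---|
| 0 | 60 | 120/60 = 2.0 | 150/60 = 2.5 | 180/60 = 3.0 |
| 60 | 120 | 180/120 = 1.5 | 210/120 = 1.75 | 240/120 = 2.0 |
| 120 | 180 | 240/180 = 1.33 | 270/180 = 1.5 | 300/180 = 1.67 |
| 180 | 240 | 300/240 = 1.25 | 330/240 = 1.38 | 360/240 = 1.5 |

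Departures from the ceiling, the target or the single control session:
- Intervention delivers 60 of 90 min in one session, P = 60: (60+60+30)/(60+30+30) = 150/120 = 1.25.
- Control receives 15 min, intervention 90 min in three sessions, P = 0: (90+90)/(15+30) = 180/45 = 4.0.
- Control splits 30 min over two sessions, intervention gives 90 min in one, P = 0: (90+30)/(30+60) = 120/90 = 1.33.
- Both a large shortfall and a split control dose (45 min in one session against 30 min in two, P = 0): (45+30)/(30+60) = 75/90 = 0.83.
- Days of passive exercises only: no difference between arms is stated, so about 1.

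If background events occur at the same constant rate in both arms, the expected ratio of background counts equals the window ratio.

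**Stopping events against the excused list.** Study intervention names ten specific events that stop a session, plus a catch-all.

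| Stops a session | On the excused list? |
|---|---|
| Low mean arterial pressure (<60 mm Hg) | Yes (listed as <65, which includes <60) |
| Heart rate out of range | Yes |
| Low oxygen saturation | Yes |
| Marked ventilator asynchrony | Yes |
| Distress | Yes |
| New arrhythmia | Yes |
| Myocardial ischaemia | Yes |
| Airway concern | Yes (as insecure airway) |
| Fall to knees | Yes |
| Endotracheal tube removal | No |

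That is 9 of 10.

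**The case against.** The restricted window is a reasoned choice: collecting every event in this population would swamp the safety data. Survival, readmissions, length of stay, delirium and ventilator-free days are collected in both arms whatever the window. The Analysis section announces no comparison of raw AE counts, events are classified by relatedness, and exposure-adjusted rates are ordinary content for the statistical analysis plan, which is not shown. All of this stands, so the point is about how the counts can be read, not about an analysis the plan has announced. The window and the reporting rule are nevertheless fixed in the protocol. Relatedness is judged by staff who know the allocation, and the other outcomes do not replace non-fatal harms of mobilisation.

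On the list, a harmonising reading exists. It speaks of AEs and not SAEs; recording may differ from reporting; and it may simply serve as the list of expected events, since the section defines unexpected by absence from such a list. This reading is possible, but the text does not state it.

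Three stronger readings are tempting and are not supported:
- **A fixed multiple, such as 1.5 to 3 times.** The protocol gives neither the length of the hold nor the number of sessions, 90 min is a target and 30 min a ceiling.
- **That the harms of mobilisation are simply exempt.** Endotracheal tube removal is not listed, and the same section says that all AEs in the window are recorded.
- **That the committee will never see these events.** Its independent members have unblinded data and a safety remit under a charter that is not shown.

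**Conclusion.** The point holds in two parts, and both should be dealt with before safety results are reported.

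Observation time for AEs and SAEs is longer by design in the intervention arm, so raw counts by arm are not comparable. The simplest figure from the protocol's own numbers is 2.0, for one session each at 90 and 30 min with no pre-session time. It is an illustration for a full active-therapy weekday. The plausible scenarios run from about 1.25 to 4, passive-only days give about 1, and this range is not a bound: a large enough shortfall in delivery removes the difference. The direction rests on the plan being followed; the size rests on assumed hold length, session number and delivered minutes.

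The reporting rule is internally inconsistent for events that cover 9 of the 10 specific stopping reasons, and it is silent on a listed event that is serious. This part needs no assumption.

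**What to change.** 1. Report AEs and SAEs by arm per session and per hour of session-plus-tail time. The denominator is each recorded session duration plus 30 min, with overlapping tails counted once. Durations are recorded daily in both arms. Show events during the sedation hold separately, because the protocol does not say that hold times are recorded. Give both rates, since a per-session rate alone does not remove the difference in session length.
2. State the arm-dependent window as a limitation wherever counts by arm appear.
3. Reconcile the two statements under Adverse event reporting, so that it is explicit whether a listed event is recorded and whether one that meets the seriousness criteria is handled as an SAE. Say how sites applied the rule.
4. Where session records allow, tabulate listed events and stopped sessions by arm for the committee's closed session and the final report. The protocol says that session duration and content are recorded, but not that reasons for stopping are, so this table may be incomplete.

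I would not ask for SAEs to be counted over a common daily period. Recruitment closed on 4 December 2014 and the trial is in follow-up, so this would need new or retrospective data collection, and its merit as a design is debatable.

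Cost: a clarification of wording, a few extra safety tables and some review of existing records.

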## Ethics and dissemination

### Consent

The consent process will depend on whether the patient has capacity to give informed consent. Eligible patients with capacity to consent will be approached by trained members of the research team who will describe the trial, including the potential risks and benefits, and provide a participant information sheet. The patient will be given time to consider whether they wish to take part in the trial and to ask any questions. The member of the research team will then invite the patient to sign the consent form. If an eligible patient lacks capacity to consent, a personal consultee will be approached in the same way as for a patient with capacity. They will be asked whether, in their opinion, the patient would agree to take part in the trial, and will be invited to sign the personal consultee declaration form. If, despite reasonable efforts by the research team a personal consultee is not available, a professional consultee will be approached and given an information sheet. The professional consultee will be the consultant responsible for the patient's care before admission to Critical Care. In determining what the person's wishes and feelings about the research would be if they had capacity, the nominated professional consultee should attempt to seek views from any family, friends or carers who may not be willing or able to act as a personal consultee. Where appropriate, other professional colleagues with an interest in the welfare or condition of the person who lacks capacity, such as other members of the care team not involved in the research, may be approached for a view. If the professional consultee deems that the patient would be willing to enter the study, they will be invited to sign a professional consultee declaration form.

### Retrospective consent

If a participant recovers from their illness and regains capacity to give consent, the same consent procedure will be carried out, as though the participant had capacity before randomisation. In these cases, a retrospective patient information sheet and consent form will be used.

### Participants who lose the capacity to consent during the trial period

The majority of critically ill patients will suffer from periods of impaired consciousness where their capacity to make informed decisions will be impaired or absent. If a patient has consented to join the study, it will be assumed that he or she would wish to continue in the trial, even if the capacity to make an informed decision is subsequently lost.

We anticipate a relatively short time window between the time of patients meeting eligibility criteria and the time that physiotherapy would be feasible. Because of the need to give patients and personal consultees sufficient time to consider participation in the trial, we will provide information sheets for patients who are judged likely to be eligible for the trial. Practically, this will include any patient who is receiving mechanical non-invasive or invasive ventilation, and in the opinion of the responsible intensive care consultant is likely to be receiving mechanical ventilation after 48 h. While this approach will allow patients and personal consultees sufficient time to consider participation in the trial, some may inevitably receive information regarding a trial for which they (or their family member) do not become eligible.

### Withdrawal of consent

Participants will have the right to withdraw from the trial at any time for any reason, or without giving a reason. Participants no longer wishing to participate in the trial may choose either to withdraw completely, or to withdraw only from the study treatment, but continue to provide follow-up data. Participants will be asked if the data collected up to the point of withdrawal may be retained, and if they are happy, for the reason for the decision to withdraw to be recorded. Personal and professional consultees also retain the right to withdraw from the trial the participant whom they represent.

### Dissemination

The results of the trial will be presented at national and international meetings and published in peer-reviewed journals. A lay summary of the results will be available to trial participants on request. An online summary of the findings, and implications of the trial, will be offered to the intensive care patient support charity ICUsteps.

### Trial status

The trial is currently in follow-up. The first patient was recruited on 16 January 2012, and the final patient was recruited on 4 December 2014.
